### 2.4. Secondary End Point

White Spot Lesions, Patient Reported Outcome Measures (PROM’s).

## 3. Statistical Analysis

The sample size was calculated using a two-sided test by comparing two independent means of control and test between groups with a statistical power of 0.80, alpha of 0.05, with an allocation ratio of 1:1 using STATA 17.0 statistical software. The mean of space closure of 3 mm in control and 5 mm in the test group with sd for control 2.5 and test 2.0 demonstrated that a sample of a least 22 subjects for both groups must be recruited (a total of 44 patients should be recruited). In order to compensate for the loss of follow-up, an increase in patient number *n* = 70 will be recruited.

A descriptive statistic will be carried out for all the indices before and after intervention with 3D and thermoformed aligners. If the data are normally distributed, a parametric test will be carried out. The non-parametric test will be used for the analysis of data that are not normally distributed. A regression analysis to determine the relationship between the dependent and independent variables and for modeling the future relationship between them.

***Safety measurements and adverse events:*** All patients will be monitored for general health and for serious adverse events related to the drug intervention. General and oral assessment including weight, blood pressure, pulse rate, skin, lymph node size, and thyroid palpation will be recorded. There will be no compensation for any adverse events or withdrawal from the study.

***Challenges and Limitations: Follow-up:*** There are chances that there will be a loss of compliance from the patient. To overcome this problem, the patient will be educated and will increase awareness in regard to the type of treatment receiving and its impact on aesthetics.

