## Abstract

Aligners are the common devices used in orthodontics for the correction of malocclusion. Various materials and techniques are employed to fabricate aligners. One of those includes thermoformed and 3D aligners. These aligners can be worn for several days, and their impact on periodontal health is not known. Therefore, the aim of our protocol is to determine the effectiveness of these aligners in correcting malocclusion and their impact on periodontal health and oral microbiome. A double-blinded randomized controlled clinical trial with a total of *n* = 60 patients will be included with *n* = 30 in each group (Test: 3D printed aligners and Control: Thermoformed). The evaluation of oral health indices such as basic periodontal examination (BPE), periodontal screening and recording (PSR) that provide the status of periodontal health will be recorded. The oral microbiome assessment will be conducted with polymerase chain reaction (PCR). The primary endpoint will be the correction of malocclusion, and the secondary end point will be the status of periodontal health and oral microbiome. The duration of follow-up for each group will be 7 days for periodontal health and oral microbiome and 6 months for the space closure of 5 mm by 3D and thermoformed aligners.

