### 1.2. Aim 2: Periodontal Health Status and Oral Microbiome

The second aim is to determine the periodontal health status during and after 3D clear aligners and thermoformed aligner therapy.

Clear aligner treatment (CAT) has been described as a secure and confident orthodontic procedure for patients. Recently, adult patients have sought a more aesthetic and comfortable orthodontic treatment than fixed appliances. To meet these needs, the treatment with transparent aligners (CAT) was introduced. The clear aligners cover the keratinized gingiva for a long period of time, and it is very important from a clinical point of view that CAT does not cause negative effects on periodontal tissues. Both conventional treatment and aligners cause a shift in the increase in anaerobes and periodontal pathogens and a decrease in commensal bacteria in the supra-gingival microbiome, but there are different types of aligners, i.e., 3D aligners and thermoformed aligners that can cause a periodontal reaction due to several factors such as the presence of systemic conditions, host resistance, and the amount and composition of dental plaque. Smoking and the patient’s lifestyle can compromise periodontal health and support. Oral hygiene procedures play a primary role in periodontal health during orthodontic treatment. Therefore, the objective is to determine the status of periodontal status and oral microbiome in 3D and thermoformed CAT.

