### 2.2. Trial Design

We propose to conduct a double-blinded randomized controlled clinical trial in patients who have >5 mm of spacing in both maxilla and mandible and cases with skeletal class I coming to the department of Orthodontics and Dentofacial Orthopaedics at Fondazione IRCCS Cà Granda Ospedale Maggiore Policlinico di Milano, SST clinics and Università degli Studi di Bari and Naples Clinica Odontoiatrica. Patients in both arms will receive adhered support and will be monitored more frequently than currently recommended by WHO guidelines. The first arm will undergo a traditional method of managing of closure of spacing by thermoformed aligners, and the second aim will be treated with thermoformed and 3D printed aligners. Eligible patients are randomized to the control arm or the intervention arm with a 1:1 ratio using a blocked randomization scheme. The patients will be followed for 6 months (Figure 1).

There will be an initial assessment with detailed case history, extra-oral and intra-oral examination, and clinical radiographs. A diagnosis and treatment plan will be framed. Pre- and post-operative samples of biofilm and saliva will be collected to determine the inflammatory and immunological response. The bridging and early colonizers such as *Fusobacterium nucleatum* (*F. nucleatum)*, pathogenic species such as *Porphyromonas gingivalis (P. gingivalis)*, microbial communities and the composition of the biofilm will be determined by ELISA and PCR. This will help to answer the questions such as if any infection is present, which bacteria colonize, whether we should use antibiotics, etc. In addition, 16 s-ribosomal RNA signatures for identification of the microbial composition of biofilm structures.

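### The article asks for the aligners' impact on periodontal health and microbiome, but every patient wears aligners under the same added support, so the trial can identify only the 3D-printed versus thermoformed difference

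*Protocol article*

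**What the plan says.** The question is worded in two ways.

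- **As impact.** The abstract gives the gap as "These aligners can be worn for several days, and their impact on periodontal health is not known" and sets out to "determine the effectiveness of these aligners in correcting malocclusion and their impact on periodontal health and oral microbiome". Section 2.1 (Preliminary Studies) again says the trial will help to establish the impact on periodontal health. Section 1.2 explains why this matters: "it is very important from a clinical point of view that CAT does not cause negative effects on periodontal tissues".
- **As status.** Section 1.2 itself states: "The second aim is to determine the periodontal health status during and after 3D clear aligners and thermoformed aligner therapy". The closing paragraph of the Introduction uses similar wording.

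The arms are 3D-printed (test) and thermoformed (control) aligners, allocated 1:1. No arm or period without aligners is described. Section 2.2 adds: "Patients in both arms will receive adhered support and will be monitored more frequently".

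For the analysis, section 3 says: "A descriptive statistic will be carried out for all the indices before and after intervention with 3D and thermoformed aligners". It then provides for parametric or non-parametric tests depending on normality, and for a regression. It does not say whether these compare time points or arms. The sample size is derived for space closure only.

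**The concern.** Asking what aligners do to the periodontium and the flora calls for a comparison with what would have happened without aligners under the same care. The trial has no such comparison. The one contrast named for the indices, before against after, also contains whatever the added support, the closer monitoring and the passage of time do.

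The randomised contrast has the opposite limit: it removes those shared influences, but it also removes any effect that both aligner types share. The article itself expects a shared effect: "Both conventional treatment and aligners cause a shift in the increase in anaerobes and periodontal pathogens".

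What is at stake is the conclusion on Aim 2. Stable indices in both arms and no arm difference could be taken as an answer to the impact question in the abstract, although the data would fit harm and no harm equally well.

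**Working it through.** **The plan's own figure.** Section 3 gives means of 3 and 5 mm, SDs of 2.5 and 2.0, two-sided alpha 0.05, power 0.80 and 1:1 allocation. The pooled SD is √((2.5² + 2.0²)/2) = 2.264. The normal approximation gives 21 per arm. The noncentral t with unequal variances gives power 0.797 at 21 and 0.816 at 22 per arm, so the stated 22 is reproduced. This figure concerns space closure and says nothing about Aim 2.

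**What the design identifies.** For a periodontal or microbiome score where higher is worse, let

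- τ = the effect of wearing aligners that is common to both types,
- θ = the additional effect of 3D-printed over thermoformed aligners,
- δ = the effect of support, attention and time, the same in both arms.

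Assuming the effects add:

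- expected change, thermoformed arm: τ + δ
- expected change, 3D-printed arm: τ + θ + δ
- difference between arms: θ

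There are two observable changes and three unknowns. The data determine θ and the sum τ + δ, but not τ. No choice of test or regression alters this, since none supplies a comparator without aligners.

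**Illustration** (assumed values in SD units, θ = 0):

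| Aligner effect τ | Support/time effect δ | Before-after change in each arm | Arm difference |
|---|---|---|---|
| 0.5 | -0.5 | 0 | 0 |
| 0 | 0 | 0 | 0 |
| 0.5 | 0 | 0.5 | 0 |
| 0 | 0.5 | 0.5 | 0 |

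The first two rows give the same data, and so do the last two. In general τ = observed change - δ. If δ may lie anywhere from -0.5 to +0.5 SD, the aligner effect is known only to within ±0.5 SD of the observed change, however many patients are recruited. The values show non-identifiability; they do not estimate how likely masking is.

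**Precision of a null arm difference.** The half-width of the 95% CI is t(0.975; 2n - 2) × √(2/n), in SDs of the change score. The article gives a minimum of 22 per arm, 30 per arm in the abstract, and 70 in total in section 3 (35 per arm):

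- n = 22: 0.61 SD
- n = 30: 0.52 SD
- n = 35: 0.48 SD

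So even for θ, which the trial can estimate, an observed difference of zero leaves true differences of about half an SD open. The article gives no SD or margin for these outcomes, so the figures stay in SD units.

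**The case against.** The strongest reply is that the Aim 2 section asks for status, not impact. Description before and after, with a comparison of arms, serves a status aim. The sentence on the shift in flora goes on to the different aligner types, and the Introduction says 3D-printed aligners need comparing with thermoformed ones. Impact can then be read as relative impact, which a 1:1 randomised trial estimates validly. An active-controlled trial with no untreated arm is an ordinary design, and the tests left open in section 3 may well be between arms.

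Much of this stands. The mismatch is with the impact and no-negative-effects wording, not with every wording of Aim 2, and a reader should not infer that the planned tests are only within arms. What remains is that the article holds both wordings, names only the before-after contrast for the indices, and has no comparator that a later analysis plan could supply.

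Some stronger readings are not supported:

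- **Regression to the mean.** The eligibility criteria in section 2.2 set no periodontal or microbiome threshold, so there is no selection on an extreme baseline of these outcomes.
- **Better cleaning.** No oral hygiene programme is described. The support in section 2.2 is undefined, and the education in section 3 concerns the treatment and its aesthetic effect. That support or attention changes the indices is possible, not documented.
- **A planned claim of safety.** The article states no such conclusion and no equivalence or non-inferiority aim. The risk lies in how results could be read.

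**Conclusion.** The point holds in a limited form. The absolute impact of aligners on periodontal health and microbiome is not identifiable here. Before-after change estimates the aligner effect plus support, attention and time effects, and a null arm difference is compatible with any effect shared by both types. The relative effect of 3D-printed versus thermoformed aligners is identifiable, with a 95% CI half-width of about 0.48 to 0.61 SD at the sample sizes given.

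This rests on three assumptions: that both arms receive the same support, that effects add, and that the unclear wording on support in section 2.2 means help with adherence. The non-identifiability does not depend on the illustrative values. A reader might infer that Aim 2 is unanswerable or that the randomised comparison is invalid; neither follows.

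**What to change.** - Align the wording in the abstract and sections 1.2 and 2.1, so that Aim 2 is the randomised difference between 3D-printed and thermoformed aligners in change from baseline of the periodontal and microbiome measures.
- In section 3, make that between-arm difference, with its 95% CI, the basis for the Aim 2 conclusion.
- Label within-arm before-after changes as descriptive, and not as evidence of aligner impact or safety.
- State that the results apply under the added support and monitoring.
- Reconcile the abstract with section 2.2, which describes the second arm as treated with both aligner types. The between-arm contrast has no clear meaning until the arms are stated consistently.

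The changes use data already planned and need no new patients or visits. The cost is a narrower claim: the trial would no longer offer an answer on whether aligners as such affect the periodontium.

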***Baseline information:*** (1) A Patient Measured Outcome Questionnaire (PROM) was completed to determine the impact of oral health on quality of life. The PROMs are dozens of tools that allow you to measure the important results for the patient, for example, cost, symptom relief, quality of care, improved oral health, and overall health. It is evaluated after each intervention. (2) Numerical rating scale (NRS) for measuring the pain of patients before and after the intervention. (3) Periodontal health status will be assessed by basic periodontal examination (BPE), Periodontal screening and recording index (PSR index), Basic Periodontal Examination (BPE) scores, Oral Hygiene Index simplified (OHIS), Saliva (Protease activity in saliva) to determine the immune-inflammatory processes by ELISA and biofilm by polymerase chain reaction (PCR). ***Inclusion criteria:*** The eligible cases will be identified during routine clinical visits. CAT is indicated in cases of slight crowding (1–5 mm), spacing problems (1–5 mm), deep overbites (Class II, div. 2), narrow arches requiring expansion, absolute intrusion (one or two teeth), severe crowding with the extraction of the lower incisor and molars requiring distal tipping. Contraindications are crowding and spacing problems greater than 5 mm, anterior-posterior skeletal problems greater than 2 mm, relationship discrepancies and centric occlusion, severely rotated and inclined teeth, open bite, dental extrusion cases, cases with more missing teeth and teeth with short clinical crowns.

Written informed consent will be obtained before the inclusion of the study. An entry form will be completed to determine the eligibility and to collect the baseline characteristics such as periapical radiographs, panoramic radiographs, models, casts, cephalometric tracings, CBCT scans, etc. Patients will be randomized in thermoformed and 3D clear aligners. All non-extraction cases except third molar extraction will be included. ***Exclusion criteria:*** Patients with deciduous and mixed dentition will not be included, and patients with systemic disease, developmental abnormalities, pregnant patients, mentally retarded patients and immunocompromised patients will not be included in the study.

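### A normality check on the outcome data chooses the test of space closure, and no baseline-adjusted comparison is fixed in advance; one pre-specified analysis in mm should replace the check

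*Protocol article*

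**What the plan says.** Section 3 (Statistical Analysis) of the protocol article gives a two-branch rule. First, "If the data are normally distributed, a parametric test will be carried out". Then, "The non-parametric test will be used for the analysis of data that are not normally distributed". It names neither test and gives no criterion for normality.

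The same section sizes the trial on means: "The sample size was calculated using a two-sided test by comparing two independent means of control and test between groups", with "statistical power of 0.80", two-sided alpha 0.05, and these inputs: "The mean of space closure of 3 mm in control and 5 mm in the test group", "sd for control 2.5 and test 2.0". The result is 22 per arm.

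It also plans a regression in general terms, with no outcome, covariates or primary role stated.

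Section 2.2 (Trial Design) lists several recruiting clinics and says "Eligible patients are randomized to the control arm or the intervention arm with a 1:1 ratio using a blocked randomization scheme". Its entry form collects "baseline characteristics such as periapical radiographs, panoramic radiographs, models, casts, cephalometric tracings, CBCT scans, etc", so space at entry can be measured.

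**The concern.** A parametric test addresses the difference in mean closure in mm. The usual two-sample rank test addresses something else: roughly, how often a patient in one arm closes more space than a patient in the other. Under the stated rule, the choice between them is made after the outcomes are seen. Two equally faithful readings of the plan could use different normality criteria and report different quantities, and one of those is not the quantity on which the sample size rests.

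Baseline spacing matters because existing space limits how much can be closed. If it predicts closure, leaving it out keeps avoidable variance in the error term. A chance imbalance between arms of 22 to 35 patients then also feeds into the estimated effect of that particular trial.

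**Working it through.** **Inputs.** From section 3: means 3 and 5 mm (difference 2), SDs 2.5 and 2.0, two-sided alpha 0.05, power 0.80, allocation 1:1, 22 per arm. From the abstract and section 3: planned totals of 60 and 70, i.e. 30 or 35 per arm. Assumed, because the documents do not give it: the correlation r between baseline spacing and closure, taken over 0 to 0.7.

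**The plan's own figure.** The normal approximation gives n = (2.5² + 2.0²)(1.960 + 0.842)²/2² = 10.25 × 7.849/4 = 20.1, so 21 per arm. With the t distribution, SE = √(10.25/n). At n = 22, SE = √0.4659 = 0.683, the non-centrality is 2/0.683 = 2.93 on 42 df, and power is 0.817. At n = 21 it is 0.798. The stated 22 per arm is reproduced.

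**Adding one covariate.** The error variance is multiplied by (1 − r²) and df = 2n − 3. Allowing for chance baseline imbalance, the variance of the treatment effect is also multiplied by 1 + 1/(2n − 4), which is 1.025 at n = 22. Example at r = 0.5: 0.4659 × 0.75 = 0.349, SE 0.591, non-centrality 3.38, power 0.910. With the allowance: SE 0.598, non-centrality 3.34, power 0.904.

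| r | 1 − r² | Power, 22 per arm | With imbalance allowance |
|---|---|---|---|
| unadjusted | – | 0.817 | – |
| 0 | 1.00 | 0.816 | 0.807 |
| 0.3 | 0.91 | 0.851 | 0.842 |
| 0.5 | 0.75 | 0.910 | 0.904 |
| 0.7 | 0.51 | 0.980 | 0.977 |

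With the allowance, break-even is at about r = 0.15.

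**At the planned totals, without losses or the allowance.** At 30 per arm, power is 0.920 unadjusted and 0.973 at r = 0.5. At 35 per arm, it is 0.954 and 0.988.

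**Adding centre as well.** Assume four sites, hence three centre terms unrelated to outcome. That makes four extra terms. The variance factor at n = 22 becomes 1 + 4/(44 − 7) = 1.108, with 38 df. Power is then about 0.77 at r = 0, 0.81 at r = 0.3 and 0.88 at r = 0.5.

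**What the normality check does.** This was simulated with 22 per arm and 8,000 runs. The gate was assumed to be Shapiro–Wilk at 5% in each arm, followed by Welch's t or Mann–Whitney. The skewed case used a gamma distribution (shape 2) scaled to the planned SDs.

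| Data | Trials sent to rank test | Type I error, gated | Type I error, fixed Welch | Power, gated | Power, fixed Welch |
|---|---|---|---|---|---|
| Normal | 10% | 0.054 | 0.052 | 0.81 | 0.81 |
| Skewed | 83% | 0.060 | 0.047 | 0.90 | 0.80 |

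**The case against.** Covariates are commonly left to an analysis plan, and none is shown here. Section 3 excludes no covariate, and its regression could include baseline spacing. Under randomisation the unadjusted comparison is unbiased and keeps its type I error. This stands: a reader might infer that the plan ignores or rules out baseline spacing, but the text shows only that it makes no commitment. The test-selection rule is different, because it is stated rather than left open.

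A reader might also infer that adjustment gives extra power for nothing. The documents do not support that. They give no correlation, about one point of power is lost at r = 0, and centre terms can use up the gain at r = 0.3. At 30–35 per arm there is less to gain.

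Nor should the check be read as a serious threat to the error rate: the simulated inflation is small. For skewed data differing by a pure shift, the gated rule even had more power than Welch (0.90 v 0.80). That would be a reason to choose a rank method in advance and size for it, not to let the data choose.

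A switch rate of 29% can be obtained by capping closure at an entry space uniform over 1–5 mm. That model brings the mean closures down to about 1.9 and 2.75 mm, so it contradicts the planned 3 v 5 mm and is not relied on here.

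**Conclusion.** The point holds in a limited form. Section 3 fixes a rule under which the outcome data decide whether the mean difference in mm, the basis of the sample size, is the quantity tested. It commits to no adjusted comparison. The main harm is that the target is open until the data are seen; the effect on type I error is slight (0.054 to 0.060 under the assumed gate).

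The benefit of adjustment depends on an unknown correlation. At 22 per arm it ranges from a loss of about one point to a gain of about 16 points at r = 0.7. The proposed model is worth adopting for its fixed target and its protection against chance imbalance, with likely extra power.

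Two conflicts come first. Section 2.3 treats 5 mm of closure as success, which reads as a binary outcome, while section 3 compares means. Section 2.2 enrols patients with spacing above 5 mm, yet its eligibility text indicates treatment for 1–5 mm and lists more than 5 mm as a contraindication. Until these passages are reconciled, neither the outcome nor the covariate's range is settled.

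**What to change.** After reconciling those passages, replace the two-branch rule for 6-month space closure with one primary analysis that applies whatever a normality check shows:

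- a linear model of closure (mm) on arm and baseline spacing (mm, measured on the entry models or casts);
- standard errors robust to unequal variances, since the planned SDs differ;
- the adjusted mean difference with its 95% CI as the reported result;
- a rank test as a sensitivity analysis only.

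Add centre terms only if randomisation is stratified by centre or the loss of degrees of freedom is accepted. Adjust the periodontal indices for their own baseline values, but with a model suited to each scale. A linear mean model is not clearly the better choice for ordinal scores such as the plaque index or BPE.

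The cost is a change of wording and the recording of entry spacing in mm. No extra patients are needed. The downside is about one point of power at 22 per arm if baseline spacing turns out not to predict closure.

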### 2.3. Primary End Point

Five-millimeter space closure: To determine the successful outcome of the 3D and thermoformed aligners, a 5 mm of space closure is considered a successful outcome.Debris Index: (The buccal scores) + (The lingual scores)/(Total number of examined buccal and lingual surfaces).Calculus Index: Calculus Index = (The buccal scores) + (The lingual scores)/(Total number of examined buccal and lingual surfaces).Oral Hygiene Index simplified (OHIS): OHIS estimates the extent and amount of debris and calculus present on the tooth in each quadrant of the mouth. It demonstrates the oral hygiene status of the mouth. It is estimated using the debris index and calculus index provided by Greene and vermillion (1964).Plaque Index: The plaque index estimates the amount of plaque on the tooth surface in each quadrant. 0—Absence of plaque, stain or debris; 1—plaque covering no more than 1/3rd of tooth surface; 2—subtle plaque more than 1/3rd but not more than 2/3rd; 3. Plaque cover more than 2/3rd of the tooth surface.Bleeding Index: A modified Sulcus Bleeding Index (mSBI) will be used to record the bleeding from the sulcus and to determine the inflammation, as it is the early indicator of inflammation (clinically).Basic periodontal examination index (BPE): Periodontal status will be determined using the BPE scoring.Root Resorption: Basic periodontal examination such as hard tissues will be conducted using a combination of bitewing and peri-apical radiographs following selection criteria for dental radiography guidelines.Biofilm/Saliva: Saliva (Protease activity in saliva) to determine the immune-inflammatory processes by ELISA and biofilm (protease activity) by polymerase chain reaction (PCR).Oral microbiome: A standard estimation of the oral microbiome will be carried out using 16S ribosomal RNA gene sequencing analysis.

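### The only adverse-event rule covers serious events related to a drug, but the trial compares two aligners, so aligner-related events, including non-serious ones, fall outside it

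*Protocol article*

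**What the plan says.** The safety text is a short paragraph within section 3 (Statistical Analysis) of the protocol article. Its opening sentence sets the monitoring rule: "All patients will be monitored for general health and for serious adverse events related to the drug intervention". The next sentence lists what is examined: "General and oral assessment including weight, blood pressure, pulse rate, skin, lymph node size, and thyroid palpation will be recorded".

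The interventions are described elsewhere. The Abstract gives the arms as "Test: 3D printed aligners and Control: Thermoformed", and section 2.2 says: "Patients will be randomized in thermoformed and 3D clear aligners".

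The article also says which harm it has in mind. Section 1.2, on the aligners' long contact with the gingiva, says that "it is very important from a clinical point of view that CAT does not cause negative effects on periodontal tissues".

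**The concern.** An adverse-event rule has to name the exposure to which events are attributed. This one names a drug in a trial of two devices. It is also the operative rule, not background text, and the article contains no other adverse-event rule.

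At stake is the attribution of events to the aligners. The trial compares a directly printed aligner with a thermoformed one, so harm from the device or its material is a natural safety question. If staff or a later analysis plan follow the sentence, they have no stated basis for classing an event as related to an aligner and no stated instruction to record a non-serious one as an adverse event.

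**Working it through.** No arithmetic applies. The check sets the relevant parts of the article side by side.

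**Step 1: what each arm receives.** The Abstract and section 2.2 describe aligners only, 3D printed or thermoformed. The analysis paragraph of section 3 itself speaks of intervention with these two aligner types. Antibiotics appear once, in section 2.2, as a question that the microbiology might help to answer. They are not a study treatment. No drug is therefore under test in either arm.

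**Step 2: apply the rule.** Its adverse-event limb sets two conditions: the event must be serious, and it must be related to the drug.

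| Event | Rule as written | Rule with drug read as aligner |
|---|---|---|
| Serious, caused by the aligner | Outside | Inside |
| Non-serious, caused by the aligner | Outside | Outside |

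The first column follows because no event can be related to a drug that is not given. The second shows that changing the one word repairs only half of the gap.

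**Step 3: look at the listed assessments.** The second safety sentence announces a general and oral assessment, but the items it names are weight, blood pressure, pulse rate, skin, lymph nodes and thyroid. All are general physical checks and none is specific to the mouth or to an aligner. The list is introduced as examples, so it does not exclude oral findings. It does not direct staff to aligner-related events either.

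**Step 4: list what is collected regardless of the rule.**

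- Gingival bleeding (section 2.3): "A modified Sulcus Bleeding Index (mSBI) will be used to record the bleeding from the sulcus and to determine the inflammation".
- Periodontal status by the basic periodontal examination (section 2.3).
- Root resorption (section 2.3): "Root Resorption: Basic periodontal examination such as hard tissues will be conducted using a combination of bitewing and peri-apical radiographs".
- Section 2.4: "White Spot Lesions, Patient Reported Outcome Measures".
- Pain on a numerical rating scale before and after the intervention (section 2.2).

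Section 3 also plans descriptive statistics for the indices before and after intervention with both aligner types. Several oral harms would therefore be available for comparison whatever the adverse-event sentence says.

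**Step 5: what those measures do not replace.** An index score gives the level of a condition at a visit. It does not record an event, grade its seriousness or judge whether the aligner caused it. An event with no matching index (a local reaction to the aligner material is an illustration of mine, not an example from the article) might be noticed under general health or the oral assessment. The text gives no rule for attributing it to the aligner.

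**The case against.** The strongest reply is that this is leftover template wording. The aligners are the only randomised interventions, the same section calls them the intervention, and staff are unlikely to attribute every event to a drug that does not exist. That is plausible. It answers the serious events only, because non-serious device events stay outside on that reading too.

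A second reply is that a condensed article leaves event definitions, grading and safety tables to the full protocol or analysis plan. That is right about detail, and missing detail is not the complaint here. The complaint is about a sentence that is present and wrong on its face, and that a later document could inherit.

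A third reply is that harms are measured as outcomes. This stands, and it limits the point. A reader might infer that safety monitoring as a whole is confined to serious drug-related events, or that the safety comparison of the two materials would contain nothing. The article supports neither inference. The same sentence also covers general health, the next adds an oral assessment, and sections 2.2 to 2.4 collect bleeding, periodontal status, root resorption, white spot lesions, patient-reported outcomes and pain.

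A reader might also try to size the problem with a confidence bound for zero events per arm. Such a bound depends only on the number of patients and would be the same after the wording is corrected, so it does not measure this defect.

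**Conclusion.** The point holds in a limited form. The adverse-event rule in section 3 names an exposure that the trial does not have. As written, it leaves aligner-related events outside related-event reporting, and it leaves the non-serious ones outside even on a charitable reading. Oral harm data are still collected, so what is deficient is the recording and attribution of adverse events, not the measurement of harm in general.

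The defect cannot be expressed as a number. It applies to every patient in both arms, because all wear aligners. It changes neither the sample size nor the space-closure comparison. It should be corrected, but it does not threaten the main result.

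The conclusion assumes that the article reflects the safety rule in force. If the full protocol, which is not shown, already defines adverse events in relation to the aligners, only the article's sentence needs correcting.

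**What to change.** Reconcile the safety paragraph of section 3 with the interventions in the Abstract and section 2.2:

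1. Replace the reference to a drug intervention with a reference to the study aligners.
2. State that serious and non-serious adverse events are recorded, each with an assessment of its relatedness to the aligner.
3. Report these events by arm, beside the oral harms already measured: bleeding index, periodontal examination, root resorption, white spot lesions and pain score.

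This needs no new examinations, no additional patients and no change to the design. The cost is a change of wording, a by-arm table that draws largely on data already planned, and slightly more event recording at the sites.
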